##### Safety & discrimination: (self)stigmatization

The stigma scale [62] is a 28-item self-report instrument for the measurement of (self) stigmatization and perceived discrimination among people with a mental illness. The scale has a three-factor structure including discrimination, disclosure and positive aspects of mental illness. Items (e.g., *I have been discriminated against in education because of my mental health problems, I do not mind people in my neighborhood knowing I have had mental health problems, People have avoided me because of my mental health problems*) are rated on a five-point Likert scale ranging from 0 = *strongly disagree* to 4 = *strongly agree*. Higher scores indicate higher perceived stigma. The S-scale has a test-retest reliability of .71 and good internal consistency (Cronbach’s α = .87) [62]. Content validity and construct validity are sufficient [63].

##### Substance use & life events: substance use

The Dutch version of the Measurement in the Addiction for Triage and Evaluation (MATE) [64] will be used to assess substance use [65]. Substances included are alcohol, nicotine, cannabis, opioids, cocaine, stimulants, ecstasy/MDMA, GHB, other hallucinogens, gambling and sedatives. Items assess the number of days on which these substances have been used in the past 30 days, and amount of use on a typical day of use. The MATE is a structured instrument that is scored on the basis of an interview with the patient. The MATE has been demonstrated to be reliable and valid, however more convincingly for Europeans [64].

In addition to the MATE, the Alcohol Use Disorder Identification Test (AUDIT) [66] and the Drug Use Disorder Identification Test (DUDIT) [67] will be used to assess alcohol and drug dependency, respectively. The AUDIT (10 items) and DUDIT (11 items) are screening instruments that assesses frequency/quantity of intake, hazardous alcohol/drug use and dependency symptoms. Scores on the AUDIT and DUDIT range from 0 to 40/44 and for both instruments the cut-off score of 10 will be used to identify alcohol and drug dependency, respectively. Psychometric properties of both instruments are satisfactory [68].

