**Methods:**

A cohort design will be used. A representative sample of community-dwelling adults with an SMI, including those in care (*n* = 650) and not in care (*n* = 150), will be followed over time. During a two-year time period, participants will be interviewed twice using a wide-ranging set of validated instruments. Interview data will be matched with administrative data about the care process, as retrieved from their patient files. Primary outcomes are changes over time in recovery, societal participation and quality of life, controlled for the occurrence of adverse life-events during follow-up. Additionally, prevalence estimates of and associations between social functioning, safety and discrimination, substance use and health indicators will be investigated.

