### Instruments and variables

#### Interview data

The current study focuses on the functioning of people with an SMI in important life-domains on the basis of five main themes: 1) sociodemographic characteristics, 2) social functioning, 3) safety and discrimination, 4) substance use and life events, 5) subjective appraisal and recovery and 6) health. Each of these themes is addressed by distinct outcomes, that will be assessed with validated instruments. The selection of instruments included matches the instrumentation of the LZA-study to a large extent, thereby enabling a third wave of the LZA study. Table 1 present an overview of all instruments included in the study protocol.

**Table 1 Tab1:** Overview of the instruments included in the questionnaire

Domains and outcome measures	Instrument	No. items
Social functioning		
Social network	Social network questionnaire (SNQ)	14
Social support	Inventory for social support (ISS)	11
Loneliness	Loneliness scale (De Jong-Gierveld)	6
Social participation	Items from health of the nations outcome scale (HoNOS)	4
Social exclusion	Social exclusion index (SEI)	19
Safety and discrimination		
Subjective safety and victimization	Integral safety monitor (ISM)	27
Discrimination	Daily discrimination scale (DDS)	9
(self)stigmatisation	Stigma scale (S-scale)	28
Substance use and life events		
Substance use and dependency	Measurement for triage and evaluation (MATE)	9
Alcohol use disorder	Alcohol use disorder identification test (AUDIT)	10
Substance use disorder	Drug use disorder identification test (DUDIT)	10
Negative life-events	List of threatening experiences (Brugha)	12
Subjective appraisal and recovery		
Quality of life	Manchester short assessment of quality of life (MANSA)	16
Recovery	Integral recovery scale (symptomatic, social, personal) (IRS)	13
	National recovery scale (personal recovery)	26
Health		
Physical health	RAND SF-36 Health Survey	12
Needs for care/support	Camberwell assessment of need short appraisal schedule (CANSAS)	25
Psychopathology severity	Brief psychiatric rating scale (BPRS)	24

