### Statistical methods

All cross-sectional socio-demographic data from both baseline and follow-up measurements will be reported in terms of percentages, means with standard deviations, and quartiles. In addition, all study measures (from the instruments administered and from the registry data) will be analyzed descriptively to provide estimates of the relevant proportions within our study population with respect to these variables as (partial) answers to research questions 2, 4 and 5.

In addition, to provide information on the association between experienced need, and the primary outcome variables (research question 1), data collected at baseline will be analyzed using multivariate regression with recovery, societal participation and quality of life as separate dependent variables and total scores on the CANSAS (i.e. number of unmet needs for care), discrimination scale, stigma scale and victimization as independent (predictor) variables. Any potential mediating effects on the associations between predictors and outcomes variables will be investigated by adding age, sex, psychiatric symptoms (BPRS-E), harmful/dependent alcohol and/or drug use (AUDIT and DUDIT respectively), physical health (RAND SF-36) and city-districts as covariates in these analyses.

To answer research question 2, relationships between the outcome measures and distinct CANSAS items, registry data concerning the care process (i.e. treatment compliance, therapeutic alliance, frequency and timeliness of care consults and self-reported support for social problems) from mental health institutions and support/welfare organizations will mainly be reported in terms of percentages and, for obvious comparisons between groups, using regression models and chi-squared tests. Their associated proportion of variance explained Nagelkerke’s R^2^, Phi for 2 × 2 tables and Cramer’s V for larger than 2 × 2 tables will be reported. Phi and Cramer’s V will be interpreted as indicating no or very weak (> 0), weak (>.05), moderate (>.10), strong (>.15) or very strong (>.25) association between variables [93]. Eta-squared and Cohen’s D will be interpreted as very small (0–.19), small (.20–. 49), moderate (.50–.79), large (.80–1.20), very large (1.20–1.99) or huge (2.0) [94].

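### The AUDIT/DUDIT cut-off of 10 is said to identify dependency, although the totals also count intake and hazardous use and the analysis section uses a wider label

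*Protocol article*

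**What the plan says.** The section on substance use within the instrument descriptions states that the AUDIT (10 items) and DUDIT (11 items) "are screening instruments that assesses frequency/quantity of intake, hazardous alcohol/drug use and dependency symptoms". It gives their purpose, that they "will be used to assess alcohol and drug dependency, respectively", and their scale: "Scores on the AUDIT and DUDIT range from 0 to 40/44". It then fixes the rule: "for both instruments the cut-off score of 10 will be used to identify alcohol and drug dependency, respectively". On accuracy it says only that the psychometric properties of both are satisfactory, with a citation.

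The Statistical methods section lists as covariates "harmful/dependent alcohol and/or drug use (AUDIT and DUDIT respectively"). It does not mention the cut-off there. Table 1 uses a third name, placing the two instruments under alcohol use disorder and substance use disorder, and gives the DUDIT 10 items.

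On reporting, the abstract says that "prevalence estimates of and associations between social functioning, safety and discrimination, substance use and health indicators will be investigated". The Statistical methods section adds that all study measures will be described so as to estimate the relevant proportions.

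**The concern.** A total that adds points for intake and hazardous use to points for dependency symptoms does not isolate dependency. The article nevertheless attaches the narrowest of its three labels to a cut-off on that total, and it gives no rule based on the dependency items and no accuracy figure for dependency. A reader of the results could not tell whether a positive participant is dependent, a harmful user, or has a use disorder in a broader sense.

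What is at stake is a descriptive result. Followed as written, the instrument section turns the share of participants who screen positive into a share who are alcohol- or drug-dependent. In a study meant to inform how ambulatory care and support are provided, that is a different and stronger statement than the instrument descriptions support.

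**Working it through.** **1. The stated scale.** Assume equal item maxima, since the article gives no item scoring.
- AUDIT: 40 / 10 items = 4 points per item; 10 × 4 = 40, as stated.
- DUDIT: 44 / 11 items = 4 points per item; 11 × 4 = 44, as stated.

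The text on the instruments is therefore coherent. Ten DUDIT items, as in Table 1, would give 10 × 4 = 40, which does not fit the stated maximum of 44.

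**2. Where the cut-off sits.** 10/40 = 25.0% of the AUDIT maximum and 10/44 = 22.7% of the DUDIT maximum. At 4 points per item, two items give at most 8 and three give at most 12, so three items can be enough to reach 10. Whether all three could be items other than dependency symptoms depends on the item split, which the article does not give. This shows that a false positive may be possible. It says nothing about how common one is.

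**3. Direction of the error.** Let p be the true prevalence of dependency, Se the sensitivity and Sp the specificity of a total of 10 or more for dependency. The reported prevalence is

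Se × p + (1 − Sp) × (1 − p).

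It exceeds p when Sp is below the break-even value 1 − (1 − Se) × p / (1 − p). None of the three inputs is in the article, so all values below are assumptions: p = 10, 20, 30%; Se and Sp each 0.70, 0.80, 0.90, 0.95 (3 × 4 × 4 = 48 combinations).

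| p | Se | Sp | Reported prevalence |
|---|---|---|---|
| 10% | 0.90 | 0.90 | 0.09 + 0.09 = 18% |
| 20% | 0.90 | 0.80 | 0.18 + 0.16 = 34% |
| 20% | 0.80 | 0.95 | 0.16 + 0.04 = 20% (no error) |
| 30% | 0.70 | 0.95 | 0.21 + 0.035 = 24.5% (understated) |

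The reported figure is above the true one in 43 of the 48 combinations, and equal or below in 5. Over the grid it runs from 11.5 to 36.5% when p is 10%, from 18 to 43% when p is 20%, and from 24.5 to 49.5% when p is 30%.

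At Se = 0.80 the break-even specificity is 0.978, 0.950 and 0.914 for p = 10, 20 and 30%. The rarer dependency is, the more specific the cut-off must be to avoid overstatement.

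The count of 43 in 48 describes the chosen grid. It is not a probability.

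**4. The labels side by side.** The instrument section says dependency, the Statistical methods section says harmful or dependent use, and Table 1 says use disorder. The second fits the described content of the totals better than the first, because it leaves room for people who score on harmful use without being dependent.

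**The case against.** The strongest reply is that a total with mixed content can still be a valid screen for dependency. The article cites work on the instruments' properties, and without the accuracy of this cut-off nobody can say that it over-counts. This stands as far as certainty and size are concerned: 5 of the 48 assumed combinations show no overstatement. It does not rescue the label, because the article itself describes a screen for a wider set of behaviours and then says that it identifies the narrower one.

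It can also be said that the Statistical methods section never ties its wording to the cut-off of 10, so the article does not strictly define one threshold in two ways. That is correct. The inconsistency is in what the measures are called. For the same reason, a reader should not infer that the covariates will be dichotomised at 10. The article does not say so, and no stated rule needs correcting there.

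A third reply is that the abstract promises prevalence of substance use and does not name dependency. But proportions are promised for all study measures, and the only classification fixed for these two instruments is the dependency one.

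Finally, a reader might infer from Table 1 that a shortened, 10-item DUDIT was administered, so that drug dependency would be under-counted. The document does not support this. The text is coherent at 11 items and a maximum of 44, nothing says that an item was dropped, and Table 1 also gives the Inventory for Social Support 11 items where its own description has 12. A counting slip in the table is the more natural reading.

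**Conclusion.** The point holds as a matter of labelling with a consequence for reporting. A screening cut-off on a mixed total is presented as identifying dependency, against the article's own description of the instruments and its wider wording in the analysis section. Reporting all positives as dependent is likely to overstate dependency. That judgement rests on assumed accuracy and prevalence values. The documents do not allow a statement that overstatement is certain, that every hazardous user would be counted as dependent, or how large the error would be. Nor do they show that 10 is a wrong cut-off, or that using the same number on both scales is an error.

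The effect is confined to descriptive proportions and to the naming of a covariate. Neither instrument contributes to the outcomes listed under Primary study outcomes: the National Recovery Scale, formal work or daytime activities, the Social Exclusion Index and the MANSA. The change is still worth making because it alters what the study can say about its participants at almost no cost.

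**What to change.** In the section on substance use, replace the statement that the cut-off identifies dependency with one that participants reaching it *screen positive for harmful or dependent alcohol or drug use*, which matches the Statistical methods section. Carry that label through the tables and text of the results. Report no prevalence of dependency from this cut-off unless its validity for dependency is shown.

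As a minor correction, check the DUDIT item count against the questionnaire and reconcile Table 1 (10) with the instrument section (11 items, range 0 to 44).

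The cost is a few words and one check, with no new data. The downside is that the study gives up a dependency prevalence from these two screens.

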##### Substance use & life events: adverse life-events

Based on Brugha’s list of threatening experiences (LTE) [69], that includes 12 distinct negative life-events, the life-time and past year occurrence of negative life-events will be assessed with *yes/no* items. Items are, for example, *having been severely ill or a victim of violence*, *the death of a parent, sibling or child*, and *having been fired*. Besides the separate items, a sum score will be computed with higher scores indicating higher exposure to negative life-events. The LTE is a valid and reliable measure with high test-retest reliability, good agreement with informant information and low internal consistency [70, 71].

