## Methods

### Study design

The Deinstitutionalization Amsterdam Client-study is a cohort study that started in December 2017. The study is planned to include approximately 800 adults with an SMI. The study population is designed to be representative for the target population of community-dwelling adults with an SMI at the city level, the level of the city-districts and the level of the city’s quarters (i.e. combined neighborhoods). To acquire a better insight into developments in the functioning and recovery of community-dwelling adults with an SMI and their associated needs for care/support, a comprehensive set of measurement instruments will be administered twice, with a two-year time interval, by means of semi-structured interviews. Also, the occurrence of adverse life-events during follow-up will be associated with developments in people’s functioning (i.e. social recovery and societal participation) over the course of time. Additionally, information about the care processes during that time will be retrieved from participants’ patient files.

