**Fig. 1 Fig1:**
[figure not shown]
Flowchart of the composition of the target population from which the study population will be sampled

In-care and not-in-care participants were recruited consecutively, to avoid duplicate recruitment attempts. The recruitment period of the in-care group, and the LZA-cohort in parallel, was December 2017–January 2021. Recruitment of participants in the not-in-care group was executed between January 2021 and January 2022. At baseline, participants were interviewed about their functioning with respect to important aspects of life (see instruments) by a pool of trained interviewers. All participants will receive a financial compensation of €15, for each interview. Interview data will be matched with information retrieved from patient files that concerns important aspects of the care process. Follow-up interviews will be held two years after the first interview and will consist of the same set of instruments as administered during interview 1. The recruitment period of follow-up interviews of the in-care cohort and the LZA-cohort will start in December 2019 to end in June 2022. Not-in-care participants will be approached to participate in interview 2 between January and September 2023.

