Research question 3 will be analyzed using data from the baseline and follow-up measurement by means of generalized linear mixed models with repeated measurements of recovery, quality of life and societal participation as dependent variables. The time between both measures will be included as a within-subjects factor. The same set of predictor variables as mentioned above will be treated as time-dependent independent variables. Additionally, the total score on Brugha’s life-events questionnaire will be included as a potential mediator to assess the effect of having experienced adverse life-events in the time period between baseline and follow-up on the associations between predictor and outcome variables. All variables will be checked for potential outliers. Missing values will be dealt with appropriately. Participants with > 80% missing values on all items will be deleted from the final dataset. For most measures, descriptive analyses will be carried out and the proportion of missing values will be reported for each variable of interest. In subsequent statistical analyses, values missing at (completely) random (i.e. MAR and MCAR) will be deleted pair wise. Values that are not missing at random (NMAR) will be imputed with either the mean, median or using multiple imputation, whichever is most appropriate. Concerning outcome measures that are a sum score of items, instructions from the instrument developers will be followed (e.g., impute missing values with the mean value of the non-missing items and calculate a sum score only if < 10% of items are missing).

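### Life events are asked for lifetime and past year only, but the analysis treats the score as events over the two years between interviews, so control for follow-up events is incomplete

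*Protocol article*

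**What the plan says.** The protocol article describes the life-events measure under Substance use & life events: adverse life-events. There, "the life-time and past year occurrence of negative life-events will be assessed with" yes/no items covering 12 kinds of event. In addition to the separate items, "a sum score will be computed with higher scores indicating higher exposure to negative life-events". The text does not say whether that sum uses the lifetime or the past-year answers.

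Under Study design, the instruments are "administered twice, with a two-year time interval, by means of semi-structured interviews". The Participants section (text after Figure 1) adds that "Follow-up interviews will be held two years after the first interview" and that they "will consist of the same set of instruments as administered during interview 1".

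The Statistical methods section states that, in the mixed model for repeated outcomes, the questionnaire's total score "will be included as a potential mediator to assess the effect of having experienced adverse life-events in the time period between baseline and follow-up". The abstract makes this part of the primary objective: "Primary outcomes are changes over time in recovery, societal participation and quality of life, controlled for the occurrence of adverse life-events during follow-up". Study design also says that events during follow-up will be related to changes in functioning.

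**The concern.** The exposure named in the analysis is the occurrence of events over a period of about 24 months. The instrument, as described, has a 12-month window and a lifetime window, and neither matches. Following the plan as written produces a variable that is not the one named in the model or in the primary-outcome statement.

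This is a data-collection choice, so an analysis plan cannot fully repair it later. A first-year event that is never asked about in a datable way is lost to the interview data. At stake is the claim that change in recovery, participation and quality of life has been adjusted for what happened to participants during follow-up.

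**Working it through.** **Windows side by side** (month 0 = baseline interview, month 24 = follow-up interview):

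| Available answer | Period covered | Relation to months 0–24 |
|---|---|---|
| Baseline, past year | −12 to 0 | none |
| Baseline, lifetime | birth to 0 | none |
| Follow-up, past year | 12 to 24 | second half only |
| Follow-up, lifetime | birth to 24 | all, mixed with everything before baseline |
| Lifetime *no* at baseline, *yes* at follow-up | 0 to 24 | first-ever event types only |

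**Months covered.** The past-year answer covers 12/24 = 50% of the interval. Some intervals may be shorter. In-care and LZA baseline recruitment ran to January 2021 and their follow-up ends in June 2022. Someone recruited last and interviewed at the close has about 17 months, of which 17 − 12 = 5 are uncovered. For the not-in-care cohort (January 2022 to September 2023) the figures are about 20 months and 20 − 12 = 8 uncovered.

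**People missed, one item.** The documents give no event rates, so assume a constant yearly probability p, independent between years. The share of people with that event in the two years whom the past-year item flags is p / [1 − (1 − p)²] = 1/(2 − p).

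- p = 0.05: 1/1.95 = 51% flagged, 49% missed
- p = 0.10: 1/1.90 = 53% flagged, 47% missed
- p = 0.30: 1/1.70 = 59% flagged, 41% missed

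**People missed, any of 12 items.** Assume further that the 12 items are independent with the same p. The yearly probability of any event is then 1 − (1 − p)¹², and the share flagged is 1/[1 + (1 − p)¹²].

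- p = 0.05: 1/1.540 = 65% flagged, 35% missed
- p = 0.10: 1/1.282 = 78% flagged, 22% missed
- p = 0.30: 1/1.014 = 98.6% flagged, 1.4% missed

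This concerns only whether a person is coded as having any event. The count of events still omits those of the first year.

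**What comparing lifetime answers would add.** Let L be the share who already answered *yes* for that event type at baseline (assumed, and unrelated to new events). A first-year-only event is recovered only in the remaining 1 − L. For one item, the combined share flagged is [p + p(1 − p)(1 − L)] / [1 − (1 − p)²]. At p = 0.10:

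- L = 0.3: (0.10 + 0.063)/0.19 = 86%
- L = 0.5: (0.10 + 0.045)/0.19 = 76%
- L = 0.9: (0.10 + 0.009)/0.19 = 57%

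So the comparison helps most for rare event types and least for common ones. The article does not plan it.

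**Direction of any bias in the coefficient.** Suppose the outcome depends on b(X₁ + X₂), where X₁ and X₂ are first- and second-year counts, and only X₂ is entered. The fitted coefficient is b[1 + cov(X₁, X₂)/var(X₂)]. With independent years this equals b. With positive correlation it exceeds b in size. Omitting X₁ leaves adjustment incomplete but does not by itself shrink the estimate.

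**The case against.** The case on the other side has several parts.

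- **The article is condensed.** Repeating the same instruments need not fix the wording of the recall period at the second interview, and a scoring rule could sit in a fuller document. That is possible. But the article states the two windows explicitly and mentions no other, so on its own text the mismatch stands.
- **Interval events are partly measured.** The past-year score covers the second year, separate items are kept at both waves, and dated crisis interventions, evictions and police contacts are collected (Administrative data). This is correct and is why the defect is incompleteness rather than absence. The registry events are not part of the score entered in the model.
- **Only one added term is affected.** Measurement of the primary outcomes, the prevalence estimates and the baseline regressions are untouched. This also stands and limits the weight of the point.

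Three stronger readings are tempting and should not be drawn. A reader might infer that 41% to 49% of exposed participants are coded as unexposed on the score. Those are per-item figures, and the any-event share is lower. A reader might infer that the life-event effect is diluted, which the algebra above does not support. And a reader might infer that job loss makes part of the covariate identical to the work outcome, or that the violence item duplicates the victimization predictor. The overlaps are only partial. Being dismissed is a past event, whereas having work or daytime activities is a current state. The article's example item joins violence with severe illness, and the victimization instrument covers 15 crime types.

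**Conclusion.** The concern holds as a mismatch between the recall window and the exposure that the analysis names. If the plan is followed, control for "having experienced adverse life-events in the time period between baseline and follow-up" is incomplete: about 12 of 24 months are not covered by the past-year score, and the lifetime score cannot separate the interval from earlier life.

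The month count needs only the stated interval and recall windows. The percentages of people missed rest on assumed event rates, constancy over time and independence. If the same people tend to have events in both years, fewer would be missed. The consequence shown is incomplete adjustment and a mislabelled variable in the longitudinal model and in the primary-outcome statement. Neither a biased outcome measure nor an attenuated coefficient is shown.

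**What to change.** - **Follow-ups still ahead when the article appeared (not-in-care, January to September 2023):** keep the lifetime and past-year items and add, for each event, a response for the period since the first interview. Add it rather than replace the existing wording. A changed window in this cohort alone would tie window length to care status in a pooled model.
- **In-care and LZA follow-ups (December 2019 to June 2022):** use the past-year score and name it *events in the year before follow-up*, both in the model and in the primary-outcome statement. As a sensitivity analysis, supplement it with first-ever events found by comparing lifetime answers at the two interviews, and with the dated registry events.
- **Pooled models:** use the past-year window for all cohorts, and state which window the total score uses.
- **Work/daytime-activity outcome:** as a sensitivity analysis only, recompute the sum without the job-loss item.

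The cost is one extra response per item in the remaining interviews and some analysis wording. The downside is that a since-baseline score will exist for only part of the sample (the not-in-care cohort, planned n = 150 of 800), so it can support a secondary analysis but not the pooled model.
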